5.2 Data analysis

Statistical analyses were performed using Stata software, Version 13 (StataCorp, College Station, TX, US). The tests were two-sided, with α=0.05. Subjects’ characteristics were described for each group as mean±standard-deviation (SD) or median and interquartile range [IQR] for continuous variables, according to statistical distribution, and numbers of physician (%) for categorical variables. To evaluate the impact of a validated information booklet, the primary analysis was performed in line with Vickers and Altman using an ANCOVA with baseline scores as independent variables. Multivariate analyses (random-effects regression models, linear for quantitative outcome and logistic for dichotomous dependent outcome) were carried out after adjusting for parameters fixed according to univariate results and clinical relevance: age, gender, experience, and center (as random effect). For other parameters, randomized groups were compared using the Chi-squared or Fisher's exact test for categorical variables, and Student's t-test or Mann-Whitney test (normality assessed using the Shapiro-Wilk test and homoscedasticity using the Fisher-Snedecor test) for quantitative parameters, as appropriate. These analyses were completed by intra-groups comparisons performed using paired t-test or Wilcoxon test for quantitative parameters, and Stuart-Maxwell test for categorical variables.

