**SYNOPSIS**

| **Title** | Measuring the impact of the French version of the Whiplash Book on both treatment approach and fears and beliefs among emergency physicians. A randomized controlled trial. |
| --- | --- |
| **Primary Investigator** | [name] |
| **Investigation Center** | CHU Clermont-Ferrand |
| **Objectives** | **Primary objective**  To determine what fears and beliefs physicians have about the consequences of whiplash. To measure the impact of a validated information booklet on emergency physicians' approach to management following a whiplash injury. |
| **Expérimental plan** | Randomized controlled study |
| **Physician number** | To assess the booklet's impact on whiplash beliefs measured by means of Whiplash belief questionnaire (WBQ), the sample size estimation was based on comparing the two study arms, with a two-sided Type-I error of 5% and statistical power of 90%. 22 subjects would be needed per randomization group in order to highlight an effect-size equaling 1 (which corresponds to a minimal difference of about 5 points for a standard-deviation between 4.78 and 5.37 concerning WBQ) under the previously described assumptions. It was eventually planned to include 24 subjects per randomization group in order to take into account any physician lost to follow up. |
| **Physician follow up** | Between 48 hours and one month |
| **Study Duration** | 4 months |
| **Study flow** | - V0 inclusion - Intervention (information leaflet) - Follow-up at least 48 hours |
| **Inclusion and non inclusion criteria** | The study was conducted involving a sample of 95 emergency physicians working in different hospital facilities in the Auvergne region, France. Hospitals were split into two groups: the six hospitals with the highest volumes, and the other seven hospitals, considered as local hospitals. |

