## 4.3.2 Bias reduction measures

Randomization :

Randomization was performed by computer by drawing lots with random block sizes and was conducted by a statistician working independently of the study. Seven hospitals were drawn to make up the intervention group (reading the booklet), whereas the other hospitals made up the control group (no specific intervention).

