# 5- STATISTICS

5.1 Subjects number

To assess the booklet's impact on whiplash beliefs measured by means of WBQ, the sample size estimation was based on comparing the two study arms, with a two-sided Type-I error of 5% and statistical power of 90%. Based on work proposed by [name] *et al.*  and an effect-size defined according to Cohen’s recommendations , 22 subjects would be needed per randomization group in order to highlight an effect-size equaling 1 (which corresponds to a minimal difference of about 5 points for a standard-deviation between 4.78 and 5.37 concerning WBQ) under the previously described assumptions. It was eventually planned to include 24 subjects per randomization group in order to take into account any physician lost to follow up.

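### Hospitals are randomised, but the primary ANCOVA treats physicians as independent, so its stated 5% error rate does not hold

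*Protocol*

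**What the plan says.** Section 4.3.2 (Randomization) makes the hospital the allocated unit: "Seven hospitals were drawn to make up the intervention group (reading the booklet), whereas the other hospitals made up the control group". The synopsis describes the hospitals as "the six hospitals with the highest volumes, and the other seven hospitals, considered as local hospitals", so there are 6 + 7 = 13 hospitals, with seven in the booklet arm and six in control.

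Section 5.2 then sets the primary analysis, citing Vickers and Altman, as one done "using an ANCOVA with baseline scores as independent variables". Baseline is the only covariate named, and the sentence mentions no hospital effect, cluster-robust variance or cluster-level degrees of freedom. The next sentence describes separate multivariate random-effects models that adjust for "age, gender, experience, and center (as random effect"). Centre is thus modelled, but only outside the analysis called primary.

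Neither the title nor section 4 calls the trial cluster-randomised.

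**The concern.** When hospitals are allocated, the effect of the booklet is estimated from differences between hospitals, and there are only 13 of them. An ANCOVA on individual physicians judges that effect against the scatter of individuals, with degrees of freedom counted in physicians. If physicians in one department resemble each other after baseline is accounted for, the standard error is too small and the test rejects too often. Any confidence interval taken from the same model would be too narrow.

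Some resemblance is plausible, because colleagues share a department and its habits. At stake is the trial's main comparison: section 5.2 promises two-sided tests at 0.05, and the named test does not deliver that. A later random-effects model that disagrees would not help, since the ANCOVA is the one designated primary.

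**Working it through.** **1. Inputs.** From the protocol: 13 hospitals, 7 v 6 (synopsis, 4.3.2); effect size 1, two-sided 5%, 90% power, 22 per arm raised to 24 (5.1); 95 physicians (synopsis). Not in the protocol, so assumed: the ICC ρ of follow-up WBQ given baseline, from 0 to 0.20, and the hospital sizes.

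**2. The plan's own figure.** n per arm = 2(z₀.₉₇₅ + z₀.₉₀)² / d² = 2(1.960 + 1.282)² / 1² = 21.01, rounded up to 22. The exact t-test power at 22 per arm is 0.8997. The figure reproduces with no design effect, so the sample size also takes physicians as independent.

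**3. Design effect, equal hospitals.** DE = 1 + (m − 1)ρ, with m = 48/13 = 3.69 or 95/13 = 7.31. The correct standard error is √DE times the naive one, and the naive test's true error is about 2[1 − Φ(1.96/√DE)]. For 48 physicians and ρ = 0.10: DE = 1 + 2.69 × 0.10 = 1.269, √DE = 1.13, error 8.2%.

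| ρ | DE, 48 | √DE | error | DE, 95 | √DE | error |
|---|---|---|---|---|---|---|
| 0.02 | 1.054 | 1.03 | 5.6% | 1.126 | 1.06 | 6.5% |
| 0.05 | 1.135 | 1.07 | 6.6% | 1.315 | 1.15 | 8.7% |
| 0.10 | 1.269 | 1.13 | 8.2% | 1.631 | 1.28 | 12.5% |
| 0.20 | 1.538 | 1.24 | 11.4% | 2.262 | 1.50 | 19.2% |

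**4. Simulation of the stated ANCOVA.** Model: arm + baseline, no booklet effect, baseline correlation 0.5, 20,000 runs per cell. The unequal sizes assumed were 7, 6, 5, 2, 2, 1, 1 v 7, 6, 6, 2, 2, 1 for 48 physicians, and 14, 12, 11, 4, 3, 2, 2 v 14, 12, 11, 4, 3, 3 for 95. True type I error:

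| ρ given baseline | 48, equal | 48, unequal | 95, equal | 95, unequal |
|---|---|---|---|---|
| 0 | 4.9% | 4.9% | 5.0% | 5.1% |
| 0.02 | 5.7% | 5.8% | 6.5% | 7.3% |
| 0.05 | 6.6% | 7.5% | 8.9% | 10.7% |
| 0.10 | 8.5% | 10.1% | 12.9% | 16.0% |
| 0.20 | 11.6% | 14.6% | 20.0% | 25.7% |

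A t-test on the 13 baseline-adjusted hospital means (11 df) stayed between 4.5% and 5.6% throughout.

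**5. From raw to conditional ICC.** The ICC that matters is the one left after adjusting for baseline. Take a raw ICC that is equal at both times and a correlation of 0.5, so the residual variance is 1 − 0.5² = 0.75.

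- Hospital effect fully persistent: ρ = ICC × (1 − 0.5)² / 0.75 = ICC/3.
- Hospital effect unrelated between the two times: ρ = ICC × (1 + 0.5²) / 0.75 = 1.67 × ICC.

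Simulated error at raw ICC 0.05 / 0.10 / 0.20 (8,000 runs per cell, range over equal and unequal sizes):

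- 48 physicians: 5.5–5.7% / 6.2–6.4% / 7.2–7.6% if fully persistent; 7.2–7.8% / 10.6–11.2% / 15.9–17.4% if not.
- 95 physicians: 6.0–6.4% / 7.6–7.9% / 9.6–10.7% if fully persistent; 11.8–11.9% / 17.4–18.8% / 28.4–28.6% if not.

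**The case against.** The strongest reply is that the plan does not ignore hospitals: section 5.2 puts centre into its random-effects models. That is true, and the criticism is confined to the model named primary. The random-effects models do not repair it. They come after the primary analysis has been fixed, their covariates are chosen partly from univariate results, and no small-sample method for 13 hospitals is given.

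A second reply is that baseline adjustment removes much of what colleagues share. This stands in part. If departmental beliefs are fully stable, two thirds of the raw ICC disappears and the inflation with 48 physicians is mild. But departmental differences that arise between the two questionnaires are not removed, and adjustment can then leave a conditional ICC above the raw one. The size of the error is uncertain in both directions; its sign is not.

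Third, the largest figures belong to 95 physicians, whereas sections 5.1 and 6.1 plan 24 per group. That is fair, so the 48-physician figures should lead.

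Fourth, section 4.3.1 speaks of physicians being drawn at random, and section 4.3.2 of random block sizes, which fit poorly with allocating hospitals. The wording needs reconciling, but section 4.3.2 is explicit about what was assigned to each arm.

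Finally, the protocol does not mention a confidence interval for the primary comparison. The remark on intervals applies to any that is reported from this model.

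**Conclusion.** The concern holds. The primary analysis does not match the allocation, and its 5% level is correct only if the ICC given baseline is zero. With 48 physicians the true error is under 6% at a conditional ICC of 0.02, about 7% at 0.05, 8.5–10% at 0.10 and 12–15% at 0.20. With 95 physicians it is roughly 9–11%, 13–16% and 20–26% at the last three values. These figures rest on an assumed ICC and assumed hospital sizes. The mismatch itself rests only on the protocol's text. It cannot be treated as detail left to an SAP, because the protocol itself fixes the primary model.

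**What to change.** In section 5.2, name as primary a linear mixed model of follow-up WBQ on arm and baseline WBQ with a random intercept for hospital, using degrees of freedom suited to 13 hospitals (Kenward-Roger or Satterthwaite). Support it with a t-test or permutation test on the 13 baseline-adjusted hospital means; the t-test has 11 df. Remove the single-level ANCOVA as the primary test, and leave the models with further covariates as secondary. Describe the trial as cluster-randomised in the title and section 4, and align section 4.3.1 with the hospital-level draw in 4.3.2.

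The cost is wording only. Place of practice is already collected (4.3.1) and centre is already used in 5.2. The p-value and any interval are likely to be less favourable. Power also falls once clustering is counted. With 24 per arm, effect size 1, equal hospitals and 11 df, and no credit for baseline adjustment, it is about 84%, 80% and 72% at ICC 0.05, 0.10 and 0.20, against the planned 90%.

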## 4.3 Design of trial to be conducted

4.3.1 For the physician

***Inclusion visit***

Screening and inclusion will be made by the physician in charge of the study.

The following data will be collected in the case report:

- Demographic data (age, gender,)

- Socio-professional data (place of practice, length and time of practice, medical training or reading)

-Personal or family history of neck pain or Whiplash

- Fear and beliefs questionnaires: WBQ, FABQ.

***Assessments****:*

Once each of the department heads and the different physicians concerned had given their agreement to take part in the study, an initial questionnaire folder (containing the WBQ and FABQ) was sent by email and by post to each of the physicians drawn by randomization. Upon inclusion, demographic data was collected from the physicians (gender, age, place of practice, and length of time in practice), as well as any personal or family history of neck pain or whiplash. The physicians were also asked how often they encountered cases of whiplash.

Information about knowledge of whiplash injury was also sought. This included continuing medical training or recent reading (within the previous 3 years), and in particular knowledge of the different severity grades established by the Quebec Task Force classification , the radiologic recommendations of the Canadian C-Spine Rule , and lastly the latest HAS recommendation on physical therapy in post-whiplash neck pain .

Once the first questionnaire folder had been completed, a second folder was then sent to all physicians participating in the study. The intervention group was instructed to complete the questionnaires at least 48 hours after the intervention, that is, after reading the information booklet. The same items were included as in the initial folder, with an additional questionnaire enabling the intervention group to qualitatively assess the information booklet. If there was no response, reminders were sent by email, then by telephone, and lastly by post.

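### Section 5.2 names baseline only in the ANCOVA and center only in the random-effects models, so no stated model of the WBQ or FABQ contains both

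*Protocol*

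**What the plan says.** Two consecutive sentences of Protocol section 5.2 define the models for the booklet's effect.

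- The primary analysis is made "using an ANCOVA with baseline scores as independent variables". It names no term for hospital.
- The random-effects models, linear for quantitative and logistic for dichotomous outcomes, are fitted after "adjusting for parameters fixed according to univariate results and clinical relevance: age, gender, experience, and center (as random effect". The list names no baseline score.

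Section 4.3.2 describes the allocation: "Seven hospitals were drawn to make up the intervention group (reading the booklet), whereas the other hospitals made up the control group". The Synopsis counts six high-volume and seven local hospitals, 13 in all.

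Section 4.3.1 places the WBQ and FABQ in the initial folder. Of the second folder it says: "The same items were included as in the initial folder". A baseline value of the WBQ and of both FABQ scales is therefore planned for every physician.

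**The concern.** Because hospitals were drawn to the arms, the model with center as a random effect is the only stated one that respects the unit of randomization, and a reader who wants an interval that allows for clustering has to turn to it. On the written list, that model compares follow-up scores alone. The protocol accepts the case for baseline adjustment in its primary analysis, citing a methods note on baseline and follow-up measurements, but does not say that the adjustment carries over to the hospital-aware model.

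Two things are at stake. The hospital-aware estimate may be less precise than the collected data allow. And with only 13 units drawn, a chance baseline gap between arms is plausible; the ANCOVA would correct for it and the random-effects model would not. The two analyses of one endpoint could then differ for a reason unrelated to hospital, age, gender or experience.

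**Working it through.** **1. The protocol's own figure.** Section 5.1 uses a "two-sided Type-I error of 5% and statistical power of 90" per cent, and states that "22 subjects would be needed per randomization group in order to highlight an effect-size equaling 1", described as "a minimal difference of about 5 points for a standard-deviation between 4.78 and 5.37 concerning WBQ". By the normal approximation:

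n per group = 2 × (1.960 + 1.282)² / 1² = 21.01, rounded up to 22.

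The stated 22 reproduces (power by the non-central t at 22 per group is 0.8997). The calculation uses neither a baseline correlation nor clustering, so this point does not alter it. Section 5.1 then adds: "It was eventually planned to include 24 subjects per randomization group in order to take into account any physician lost to follow up". That gives 2 × 24 = 48.

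**2. Precision.** Let r be the baseline/follow-up correlation of the score. The protocol does not give r, so a range is assumed. Adjusting for baseline multiplies the residual variance by 1 − r², so omitting it widens the interval by a factor of 1/√(1 − r²).

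| Assumed r | 1 − r² | Width ratio without baseline |
|---|---|---|
| 0.3 | 0.91 | 1.05 |
| 0.5 | 0.75 | 1.15 |
| 0.7 | 0.51 | 1.40 |

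**3. Power at the protocol's target of 1 SD, with hospital as the unit.** Further assumptions are an ICC of 0.05 (not in the protocol), equal hospital sizes, balanced arms, no loss from the 48, and the same factor 1 − r² between and within hospitals. Degrees of freedom are 13 − 2 = 11.

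- Mean hospital size: m = 48/13 = 3.69.
- Design effect: 1 + (3.69 − 1) × 0.05 = 1.13.
- Standard error in SD units: √(4/48 × 1.13 × (1 − r²)). Without baseline this is 0.307, or 1.54 points at an SD of 5.
- Power comes from the non-central t with non-centrality 1/SE.

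| Analysed, assumed ICC | No baseline | r = 0.3 | r = 0.5 | r = 0.7 |
|---|---|---|---|---|
| 48, 0.05 | 0.84 | 0.87 | 0.93 | 0.985 |
| 48, 0.10 | 0.80 | 0.83 | 0.90 | 0.97 |
| 95, 0.05 | 0.97 | 0.98 | 0.99 | >0.99 |

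The last row uses the 95 physicians named in the Synopsis (m = 7.31, design effect 1.32).

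**4. Chance baseline imbalance.** With 48 physicians and ICC 0.05, one standard error of the baseline gap between arms is SD × √(4/48 × 1.13): 1.47 points at SD 4.78 and 1.65 at SD 5.37. An unadjusted model carries r times that gap into the estimate: 0.73 to 0.83 points at r = 0.5 and 1.03 to 1.16 at r = 0.7, against the 5-point target. This is the same variance already counted in steps 2 and 3, seen in a single trial. It is not an additional loss.

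**The case against.** The strongest reply is that the list is not closed. It also omits the randomized arm, and read literally the models would then estimate no booklet effect. If the arm is understood, baseline may be understood too, and the sentence can be taken as adding terms to the ANCOVA just described. This stands as a possible reading. A reader might infer that the protocol deliberately discards baseline; the text does not say that. Nor does it say that baseline is kept, and the two readings give different analyses.

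A second reply is that the full specification of a supporting model belongs in the SAP. That would hold had the protocol been silent. Here it names an adjustment set, and that set leaves baseline out.

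Three stronger claims should not be made.

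- A reader might call baseline the strongest covariate collected. The protocol gives no correlation or explained variance to support this.
- A reader might infer bias. Under randomization the baseline gap is random error.
- A reader might extend the point to the logistic models. The protocol does not expressly place the clinical case in the first folder, so a baseline answer is not shown to exist. The factor 1 − r² also does not carry over to logistic regression, where adding a prognostic covariate changes the conditional odds ratio itself.

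Finally, the primary ANCOVA's lack of a hospital term is a weightier gap in the same section. One model with arm, baseline and hospital would close both. That does not remove this point: anyone who turns to the random-effects model for clustering would, following the text, leave baseline out.

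**Conclusion.** The point holds as a defect of specification in the linear models for the WBQ and both FABQ scales: no stated model has both baseline and hospital, and the text leaves open whether the hospital-aware one keeps baseline. If it does not, the loss is precision and protection against chance imbalance.

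The size depends on two quantities that the protocol does not give, r and the ICC. At r = 0.3 the gain from baseline is small. At r = 0.5 or more and ICC 0.05, it brings the hospital-aware analysis of 48 physicians from below the planned 90% power to above it; at ICC 0.10 and r = 0.5 it reaches about 90%. If 95 physicians are analysed, power at the 1 SD target is ample either way and only the narrower interval remains as a benefit. The correction is worth making because the data are already planned and the change is very small.

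**What to change.** In section 5.2, for the linear random-effects models (WBQ, physical activity FABQ and work FABQ), put the baseline value of the same outcome at the head of the adjustment list, before age, gender, experience and center as a random effect. If the list was always meant to extend the ANCOVA, this only records the intention.

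Leave the logistic models out of this change, unless the protocol first establishes that the clinical case is answered at baseline.

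Cost: one phrase and one degree of freedom per model. No new data and no added burden on the physicians.

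### The simple two-sample tests in section 5.2, on the natural reading meant for FABQ and management, ignore that hospitals were randomised and omit the FABQ baseline; the planned random-effects models are assigned to no outcome

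*Protocol*

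**What the plan says.** Allocation was by hospital. Section 4.3.2 reads: "Seven hospitals were drawn to make up the intervention group (reading the booklet), whereas the other hospitals made up the control group". The Synopsis counts "the six hospitals with the highest volumes, and the other seven hospitals, considered as local hospitals", so there are 13 hospitals, 7 against 6.

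Section 5.2 then sets out four layers of analysis:

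1. A primary ANCOVA with baseline scores as covariates. No hospital term is stated and the outcome is not named.
2. Random-effects models, linear or logistic by type of outcome, adjusted for age, gender and experience, with centre as a random effect. No outcome is named, and a baseline score is not among the listed covariates.
3. "For other parameters, randomized groups were compared using the Chi-squared" or Fisher test, and the t-test or Mann-Whitney test for quantitative items, the choice depending on normality and variance pre-tests.
4. "These analyses were completed by intra-groups comparisons performed using paired t-test or Wilcoxon test for quantitative parameters", with a Stuart-Maxwell test for categorical items.

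Section 4.2.3 makes FABQ and management (a clinical case) secondary outcomes. Section 4.3.1 lists under the inclusion visit "Fear and beliefs questionnaires: WBQ, FABQ", and the second folder repeats the items of the first. Section 5.2 names neither FABQ nor management.

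**The concern.** The third layer is a stated rule, not a missing detail, and it does not fit the design. Physicians in one hospital share an allocation and probably share habits and training. A test that counts them as independent understates the standard error of the arm difference. For FABQ, a follow-up-only comparison also gives up precision that the baseline would supply.

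The fourth layer raises a separate issue. A before-after p-value in each arm does not compare the arms. Both arms answer the same questionnaires twice, so a shift from re-testing could appear in either. A change that is significant in one arm and not in the other is not evidence of a booklet effect.

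At stake are the secondary conclusions. They include the treatment approach, which is in the trial title.

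**Working it through.** **Inputs from the Protocol.** Two-sided 5% level (5.1, 5.2); 90% power and effect size 1 (5.1); 22 per arm, raised to 24 for losses, so 48 in all (5.1, 6.1); 95 physicians (Synopsis); 13 hospitals, 7 v 6 (Synopsis, 4.3.2).

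**Assumed, because the Protocol gives no value.** ICC 0.01 to 0.20; FABQ correlation between baseline and follow-up 0.3 to 0.7.

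**Step 1: the plan's own figure.** n per arm = 2 × (1.960 + 1.282)² / 1² = 21.0, rounded up to 22. The noncentral-t power at 22 per arm is 0.900. The stated 22 is reproduced, as an individual-level calculation with no design effect. For "a minimal difference of about 5 points for a standard-deviation between 4.78 and 5.37 concerning WBQ", the same formula gives 20 per arm at the lower SD and 25 at the upper.

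**Step 2: which outcomes fall under the simple tests.** Subject characteristics have their own descriptive sentence. The within-arm tests are said to complete the preceding analyses, and paired tests are possible only for items measured twice. The repeated scores are WBQ and FABQ. Stuart-Maxwell needs repeated categorical answers, for which the clinical case or the knowledge items are candidates. FABQ and management are therefore the natural reading, but an inferred one.

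**Step 3: true error of a test that ignores hospital.** Design effect DE = 1 + (m − 1) × ICC, with m = 48/13 = 3.69 or 95/13 = 7.31. Actual two-sided error ≈ 2 × [1 − Φ(1.96/√DE)].

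Example with 48 physicians and ICC 0.10: DE = 1 + 2.69 × 0.10 = 1.269; 1.96/√1.269 = 1.74; error ≈ 8.2%.

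The formula was checked by simulating a t-test with 7 v 6 hospitals of near-equal size (20,000 runs per row):

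| Physicians | ICC | DE | Formula | Simulation |
|---|---|---|---|---|
| 48 | 0.01 | 1.027 | 5.3% | 5.4% |
| 48 | 0.05 | 1.135 | 6.6% | 6.8% |
| 48 | 0.10 | 1.269 | 8.2% | 8.4% |
| 48 | 0.20 | 1.538 | 11.4% | 11.9% |
| 95 | 0.01 | 1.063 | 5.7% | 5.6% |
| 95 | 0.05 | 1.315 | 8.8% | 8.9% |
| 95 | 0.10 | 1.631 | 12.5% | 12.6% |
| 95 | 0.20 | 2.262 | 19.3% | 19.8% |

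**Step 4: cost of omitting the FABQ baseline.** ANCOVA residual variance = (1 − ρ²) × follow-up variance, that is 0.91, 0.75 and 0.51 of it at ρ = 0.3, 0.5 and 0.7. As an illustration, take 24 per arm and a standardised difference of 0.6, ignoring clustering. Power is 0.53 without the baseline and 0.57, 0.65 and 0.81 with it.

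**The case against.** The strongest reply is that section 5.2 already plans models with centre as a random effect. WBQ is a quantitative score, so the logistic branch must serve some other outcome, plausibly management. This stands. A reader might infer from the simple-tests sentence that nothing outside the primary analysis accounts for hospital, and the text does not support that. The models do not close the gap, however. They are assigned to no outcome and given no precedence over the simple tests. The logistic branch covers only dichotomous items, whereas Stuart-Maxwell suggests that answers with more than two categories are expected.

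Other parts of the reply also stand:

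- The other parameters are undefined and could mean knowledge or training items. The plural in the ANCOVA's baseline scores could be stretched to cover FABQ.
- It would be wrong to say that the FABQ baseline is discarded. The paired tests use it; it is absent from the simple between-arm test.
- It would be wrong to infer that the primary analysis handles hospital and the secondary ones do not. The primary ANCOVA states no hospital term either.
- The within-arm tests are supplementary, and nothing says that benefit will be claimed from them. Section 6.2 does expect a significant improvement, which is the kind of statement such p-values invite.
- At ICC 0.01 the error is close to nominal, and the figures near 20% need both ICC 0.20 and 95 physicians, while the planned size is 48.

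Finally, a statistical analysis plan, not shown here, may assign outcomes to models. That would settle the ambiguity, but the rule in section 5.2 would still be stated wrongly for this design.

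**Conclusion.** The point holds in a conditional form. If the simple tests are the main analysis of FABQ and management, as section 5.2 most naturally reads, they are anti-conservative under hospital randomisation, and the FABQ comparison is less precise than the collected data allow. For an ICC of 0.01 to 0.20, the true error of a nominal 5% test runs from about 5% to 12% with 48 physicians and from about 6% to 20% with 95. These sizes rest on an assumed ICC and near-equal hospital sizes, and the simulation was for the t-test. The precision loss rests on assumed correlations.

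The Protocol does not show that every secondary analysis ignores hospital, because the centre random effect is planned for outcomes it does not name. That within-arm p-values do not test the booklet holds however the other parameters are read. The matter should be corrected; it concerns secondary outcomes and does not by itself undermine the trial.

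**What to change.** In section 5.2:

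- **FABQ, both scales:** make the between-arm analysis a linear mixed model with arm, baseline FABQ and random hospital, with a small-sample degrees-of-freedom correction for 13 hospitals.
- **Dichotomous clinical-case items:** use the logistic model with random hospital that is already planned. Add the baseline answer only if the case was in the first folder; section 4.3.1 describes that folder as containing WBQ and FABQ and does not mention the case.
- **Multi-category items, or an unstable logistic model:** use a hospital-level or other cluster-adjusted comparison.
- **Reporting:** base secondary conclusions on between-arm differences with 95% confidence intervals. Present within-arm changes descriptively, not as evidence of a booklet effect.

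Dropping the normality and variance pre-tests is optional.

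The cost is a rewording, a little more analysis work and somewhat wider intervals once hospital is accounted for. No new data are needed.
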